Malaysian citizen.	Having severe health conditions (e.g., respiratory and cardiovascular disease requiring oxygen support such as severe asthma, Chronic Obstructive Pulmonary Disease, heart failure and congenital heart diseases).
Age 18 years old and above.	Residing temporarily (less than 2 years).
The head of the household, or the person who contributes to, or influences health-related decisions for the household.	Intending to relocate to a different village within the next 2 years.
Live in a household with more than two members.	
Able to converse, read and write in Malay.	

Sampling, randomization, allocation, and blinding

The study utilizes a multistage sampling approach with computer-generated randomization for the allocation of villages into the intervention or control arm. Due to potential variability in participant numbers and logistical challenges, simple randomization is employed over block randomization for its flexibility and straightforward, unbiased allocation. The entire sampling, randomization, and allocation process is conducted independently by an external health professional with research experience.

First, two districts in Selangor are randomly selected from the eligible pool. Within each district, four villages are randomly chosen. These villages are then divided, with two randomly allocated to the intervention group and two to the control group in each district (i.e., each district has two intervention villages and two control villages). This approach aims to achieve homogeneous sociodemographic groups among the households. Household recruitment in each village is voluntary, facilitated by JAKOA, village leaders, and committees, targeting 12 households per village.

Given the nature of the intervention, the authors are inevitably aware of group allocation. Procedures are identical for both groups, and research assistants are not provided with information about the study sequence or allocation; hence, they remain uninformed about group assignment. Participants in both groups will remain blinded to their allocation throughout the study.

Intervention

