Data collection will be conducted by using the Household Outbreak Preparedness Evaluation (HOPE) questionnaire, administered at four intervals: (i) before the intervention (T0); (ii) immediately after the intervention, with the intervention group having received both the X-SIAGA intervention and educational brochures and the control group having received educational brochures only (T1); (iii) at one month post-intervention (T2); and (iv) at three months post-intervention (T3). The HOPE questionnaire is an adapted and translated instrument based on prior studies on household preparedness for outbreaks and general disasters [15,24]. Validation of the HOPE questionnaire will be published elsewhere. The questionnaire is self-administered, with assistance available from trained research assistants and representatives of the village committee if participants require support.

Outcome measures

The scoring for the HOPE questionnaire follows Sumaja’s methods [24]. The primary outcome measure, the Household Outbreak Preparedness score, represents the equally weighted average of the Cognitive Preparedness and Preparedness Behavior scores. By using Sumaja’s preparedness matrix [24], scores will be normalized to a scale of zero to one, and a cut-off value of 0.5 at the x- and y-axes will categorize households’ outbreak preparedness into four groups: Fully Prepared, Committed, Aware, and Unprepared.

Secondary outcome measures include the Cognitive Preparedness and Preparedness Behavior scores. The Cognitive Preparedness score assesses household knowledge, attitudes, and health beliefs, while the Preparedness Behavior score evaluates the skills acquired and practices adopted by households to prepare for potential Disease X and outbreaks.

Control of bias

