To prevent contamination bias, the study ensures sufficient geographical separation between intervention and control villages to minimize interactions among participants from different groups. Prior to recruitment, the research team held meetings with village leaders and committee members, in the presence of JAKOA officials, to explain the X-SIAGA intervention, emphasize the importance of strict confidentiality, and discourage discussions about the intervention. These leaders and committee members then conveyed this information to eligible participants during household recruitment. All participants will again receive a detailed explanation of the privacy and confidentiality policy when expressing interest in joining the trial, and only those who provide consent will be enrolled. To mitigate attrition bias, the study will employ an Intention-to-Treat (ITT) approach. Additionally, to sustain motivation and engagement, perishable goods will be offered as incentives at each stage of data collection.

Statistical methods

The statistical analysis for this study will be carried out by using the IBM SPSS Statistics for Windows, Version 26 (Released 2018; IBM Corp., Armonk, New York). Descriptive statistics will include frequency and percentages for categorical data and mean and standard deviation for numerical data.

To compare baseline sociodemographic characteristics between the intervention and control groups, a Pearson Chi-Square test will be utilized for categorical variables, while an Independent Samples t-test will be used for continuous variables. To evaluate changes over time from T0 to T3 between and within the groups, a repeated-measures analysis of variance will be conducted. To assess variation in results between and within the groups across the different time points, while also controlling for potential confounding variables, a generalized estimating equation will be utilized.

Statistical analyses will use a two-tailed test to evaluate the superiority hypothesis. The null hypothesis states that there is no difference between the X-SIAGA intervention package and standard educational brochures. A significance level of 0.05 will be applied.

Data management

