To manage missing data and outliers, corrective actions will be taken to recover or validate entries. The research team will reach out to the participant for clarification and ensure accurate data entry. The Last Observation Carried Forward method will be utilized for uncontactable dropouts. A sensitivity analysis will be performed to determine how using the ITT approach with imputed data might affect study conclusions.

During the research, data will be managed carefully to ensure privacy and confidentiality. All data generated will be de-identified and anonymous, with the principal investigator being the only one with access to identifiable information. Results will be presented in aggregated form to prevent reidentification of any individual or address. The findings from this study will be disseminated as conference abstracts, posters, and presentations, and manuscripts will be developed for publication from the study findings.

Individual participant data will be shared only upon reasonable request and will require approval from UiTM and the Ministry of Health Malaysia (MOH). These datasets will not contain any identifiers. Participants may request access to their own results and to the general study findings, but not to other participants’ data.

All data will be stored in soft-copy format on a password-protected computer and archived on a secure, password-protected flash drive to prevent data loss or damage. Data will be retained for seven years after publication, after which it will be securely destroyed by deleting and overwriting the files.

Trial registration, ethics approval, and consent to participate

This study has been registered at ClinicalTrials.gov (NCT06539845) and has received ethical approval from the National Medical Research Registry/Medical Research and Ethics Committee (Ref: 24-01859-NQ7) and the Universiti Teknologi MARA Research Ethics Committee (Ref: REC/10/2024 (PG/FB/33)).

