## Discussion

This study will be a two-arm cluster randomized trial evaluating the effectiveness of the X-SIAGA intervention. The X-SIAGA intervention is a novel, theory-based intervention package tailored for the Orang Asli community to enhance their household preparedness for Disease X and future outbreaks. This intervention aims to empower the community to respond effectively to infectious disease outbreaks, including novel threats, while waiting for intervention from health authorities, thereby reducing the negative impact and mortality rates associated with such events.

X-SIAGA addresses a crucial gap in micro-level preparedness. While numerous initiatives focus on macro-level preparedness, outbreaks invariably begin and spread within communities before being detected by authorities. Marginalized populations, such as Indigenous communities, are often disproportionately affected due to pre-existing vulnerabilities and limited access to resources [17,19]. Most existing community preparedness programs in Malaysia target floods, with no known initiatives addressing outbreak preparedness at the household level, especially among the Orang Asli [9]. X-SIAGA is pioneering as the first outbreak preparedness program in Malaysia tailored to the needs of the Orang Asli.

The study’s findings are anticipated to provide essential insights and evidence for the development of targeted health interventions, significantly contributing to enhancing public health preparedness and resilience, especially within marginalized communities.

While X-SIAGA has its strengths, there are notable limitations to the study. The expectation of immediate personal benefits among the Orang Asli population may pose challenges in participant recruitment and retention. The potential Hawthorne effect cannot be fully dismissed; mitigation efforts will include assuring participants that responses will not incur any penalties.

The X-SIAGA intervention will be conducted in a single session, with a follow-up period restricted to three months due to resource and time constraints. While some studies have shown that community interventions delivered in one session can lead to beneficial outcomes in a short timeframe [29,30], expecting sustained change from a single session may not be realistic, and short-term follow-ups might overlook the long-term effects of the intervention.

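### Village committee representatives, who promoted the study and were briefed on X-SIAGA, may help complete the only outcome questionnaire; this could bias the comparison to the extent that their influence differs by arm

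*Protocol article*

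**What the plan says.** All outcomes come from one instrument, the HOPE questionnaire, given at T0, T1, T2 and T3. Under Data collection, "The questionnaire is self-administered", "with assistance available from trained research assistants and representatives of the village committee if participants require support". Under Outcome measures, the primary score "represents the equally weighted average of the Cognitive Preparedness and Preparedness Behavior scores", and those two component scores are the secondary outcomes. They cover knowledge, attitudes, health beliefs, skills and practices.

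The same committees appear elsewhere in the protocol article:

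- **Recruitment:** committee members commit to the study and then promote it to eligible villagers. A list of interested and eligible people goes to the research team.
- **Control of bias:** before recruitment, "the research team held meetings with village leaders and committee members, in the presence of JAKOA officials, to explain the X-SIAGA intervention". Confidentiality was stressed and talk about the intervention was discouraged.
- **Consent:** committee representatives may assist here too.

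The blinding text, under Sampling, randomization, allocation, and blinding, covers research assistants and participants. It says nothing about committee representatives. Control of bias addresses contamination, attrition and engagement, but not help with the questionnaire.

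**The concern.** A respondent who needs help may report beliefs and household practices in the presence of a local figure who took the study on, recommended it and knows what X-SIAGA is. Two mechanisms are plausible: answers that please the helper, and help that turns into prompting. No other outcome measure is described against which the self-report could be checked.

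The influence would act at village level, which is the unit of randomisation. One helper's style can affect many of the 12 households targeted in a village, and there are only four villages per arm. Such an influence does not average out over households. If it were stronger after the programme in intervention villages than after the brochure in control villages, part of it would be read as an effect of X-SIAGA.

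**Working it through.** The plan gives no figure for this point, so there is none to reproduce. The check has two parts.

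**1. The text side by side**

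| Question | Research assistants | Committee representatives |
|---|---|---|
| May help with HOPE? | Yes (Data collection) | Yes (Data collection) |
| Stated to be trained? | Yes | No |
| Stated to be uninformed of allocation? | Yes (Sampling, randomization, allocation, and blinding) | No statement |
| Told about X-SIAGA? | Yes, trained and help deliver it (Intervention) | Yes, briefed before recruitment (Control of bias) |
| Promote the study locally? | Not stated | Yes (Recruitment) |

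The article does not say that committees are told their village's arm. It does say that the one-day programme takes place in the intervention villages themselves. A committee that has been briefed on X-SIAGA could therefore work out its arm by seeing whether the programme takes place. That is an inference, not a statement in the article.

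**2. What reaches the arm contrast**

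Let p be the share of questionnaires completed with committee help in an arm, and s the average shift that such help gives to the score. At one visit:

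bias in the arm difference = p(intervention) × s(intervention) − p(control) × s(control)

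For change from baseline, subtract the same quantity at T0. An influence that is already present at T0 and constant drops out. One that grows after the programme does not.

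The article gives neither p nor s. With assumed p of 0.10, 0.25 and 0.50 and assumed s of 0.2 and 0.5 SD, the shift p × s in one arm's mean is:

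| p | s = 0.2 SD | s = 0.5 SD |
|---|---|---|
| 0.10 | 0.02 SD | 0.05 SD |
| 0.25 | 0.05 SD | 0.125 SD |
| 0.50 | 0.10 SD | 0.25 SD |

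Each entry is the bias in the contrast only if the other arm has no shift at all. If both arms have p = 0.25 and s = 0.5 SD, the bias is 0.125 − 0.125 = 0. The table shows how the bias would scale; it is not an estimate.

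**The case against.** The strongest case on the other side is this. The provision is the same in both arms and at every visit, so an equal pull cancels. Help is given only when needed, and Table 3 requires participants to be "Able to converse, read and write in Malay", so p may be small. The Introduction does report lower education levels in this population, so some need for local help with a translated instrument is credible. The article does not say what assistance consists of; the full protocol may restrict it. The Discussion also admits that people with village roles may sway the findings. All of this stands and limits the likely size. The last point is only a partial answer, because it is made about non-random recruitment and not about outcome measurement.

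A further objection bears on the remedy. Under Intervention, the research assistants help deliver X-SIAGA. Making them the only helpers does not give blinded assessment, and it leaves a link to the intervention arm. This is correct, and the fix has to deal with it.

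Three stronger readings are tempting, but the article does not support them:

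- **A breach of confidentiality.** Data management describes de-identified data "with the principal investigator being the only one with access to identifiable information". That concerns handling of the generated data, not who may be present at completion. Read more widely, it would rule out the research assistants as well.
- **A contradiction of the Hawthorne safeguard.** The Discussion says "mitigation efforts will include assuring participants that responses will not incur any penalties". Nothing says that committee members penalise or record answers.
- **A demonstrated inflation of benefit.** The article does not say that committees endorse the programme in intervention villages. It says only that it is held there and delivered by the authors with research assistants.

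**Conclusion.** The point holds as an avoidable weakness in how the outcome is measured. People who took on and promoted the study, and who know the intervention, may help complete the questionnaire behind every outcome, and no stated safeguard covers them in that role. Village-level reporting bias is plausible.

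It distorts the comparison only to the extent that it differs between arms. A difference is plausible because only intervention villages receive the one-day programme; if so, the likelier direction is towards an exaggerated benefit, but neither the difference nor its direction is established. The size cannot be derived from the article. The range of 0.02 to 0.25 SD rests wholly on assumed shares and shifts, with no shift in the other arm. No stated figure changes and no other passage is contradicted. The case for acting is that the remedy costs very little.

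**What to change.** 1. In Data collection, remove committee representatives from questionnaire help at T0 to T3, and keep them where they cannot see answers.
2. Limit help to the trained research assistants who already have this task, reading items word for word from a fixed script without explanation or prompting.
3. Because these assistants also help deliver X-SIAGA, use for questionnaire help, where possible, existing assistants who did not deliver the programme in that village.
4. Record each assisted questionnaire by visit. Tabulate the counts by arm and village, and repeat the primary analysis without the assisted questionnaires as a sensitivity analysis. Need for help after T0 may itself depend on arm, so this should not replace the main analysis.

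Committee roles in recruitment and consent are unchanged.

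The cost is one clause, a site instruction, a tick-box and some rostering. Sessions may run slightly longer, and participants who would prefer a local helper lose some support. The number of assistants is not given, so item 3 may not be achievable at every visit; item 4 would still show how often help was used in each arm.

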This study adheres to the Malaysian Code of Responsible Conduct in Research to ensure data confidentiality and compliance with ethical standards. Engagement with the indigenous community throughout the study is conducted in a manner that is mutually beneficial, respectful, and sensitive to cultural norms. Participants are provided with a study information sheet that offers detailed information about the study’s purpose, procedures, and what participation entails. This information is given during recruitment advertisements and again before participants give consent.

Consent will be secured through written consent forms from participants before joining the study. Informed consent will be obtained by the research team, with assistance from representatives of village committee members provided as needed to ensure full understanding of the information. Investigators are available to answer any questions, and ample time is given for consideration of involvement in the study. All prospective participants are informed that participation is entirely voluntary. Withdrawal from the study is permitted at any time without any negative consequences, and there is no requirement to disclose reasons for withdrawal.

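### Intention-to-treat is the stated guard against attrition bias, but one of the two between-arm analyses (repeated-measures ANOVA) drops households that withdraw while still contactable, because LOCF is worded only for uncontactable dropouts

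*Protocol article*

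**What the plan says.** Four statements in Materials and methods bear on this point.

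- **Control of bias:** "To mitigate attrition bias, the study will employ an Intention-to-Treat (ITT) approach". This is the only analytic safeguard named there against attrition bias. The incentives mentioned in the same section act on retention.
- **Data management:** "To manage missing data and outliers, corrective actions will be taken to recover or validate entries", by going back to the participant. Then: "The Last Observation Carried Forward method will be utilized for uncontactable dropouts". No other imputation rule is given. The paragraph ends: "A sensitivity analysis will be performed to determine how using the ITT approach with imputed data might affect study conclusions".
- **Statistical methods:** two analyses compare the arms over time. The first: "To evaluate changes over time from T0 to T3 between and within the groups, a repeated-measures analysis of variance will be conducted". The second covers variation between and within groups across time points: "while also controlling for potential confounding variables, a generalized estimating equation will be utilized". Neither is named primary.
- **Trial registration, ethics approval, and consent to participate:** "Withdrawal from the study is permitted at any time without any negative consequences", and no reason need be given.

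Under Sample size, the article anticipates about 30% attrition and plans 96 households, which is 48 per arm.

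**The concern.** The article fixes a principle (ITT), the scope of an imputation rule (uncontactable dropouts) and a model (repeated-measures ANOVA), and the three do not fit together for every household. Loss of contact is only one route to a missing score. A household may tell the team that it is withdrawing, or miss T2 and return at T3. Neither is an uncontactable dropout, so LOCF as worded does not reach them.

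Classical repeated-measures ANOVA works on units with complete data, so it removes such a household at every visit, including those it attended. If households that withdraw differ from those that stay, and differ in one arm more than in the other, the arm contrast among completers is biased. That is possible here: one arm receives a one-day programme with a take-home booklet and plan, the other only brochures. This point is separate from whether LOCF is a good imputation, since it concerns the households that LOCF does not reach.

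**Working it through.** **1. What happens to each kind of missing visit, as written**

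| Household | Stated handling | Repeated-measures ANOVA | GEE |
|---|---|---|---|
| Uncontactable dropout | LOCF | kept, with carried-forward scores | kept |
| Missed visit, entry recovered | recovery | kept | kept |
| Missed visit, entry not recovered | none stated | removed at all visits | observed visits kept |
| Withdrawn but contactable | none stated | removed at all visits | observed visits kept |

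The last two rows are the problem. The removal follows from the method. The article does not state it as a rule.

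**2. The plan's own sample size, reproduced**

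Inputs from Sample size: Z values 1.96 and 0.842, Δ = 15.97, σ² = 138.949, n = 54, ρ = 0.048.

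- Before clustering: (1.96 + 0.842)² × 2 × 138.949 / 15.97² = 8.555.
- Design effect: 1 + 53 × 0.048 = 3.544.
- Households per arm: 8.555 × 3.544 = 30.32 (stated: 30).
- With 30% attrition: 31 / 0.7 = 44.3, rounded up to 45 (stated: 45).

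**3. Households kept by the ANOVA**

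The split of the 30% is not given, so the contactable, unimputed share s is an assumption. Kept per arm = 48 × (1 − 0.30 × s). Power is the normal approximation with the plan's own Δ, σ² and design effect of 3.544: Φ[(Δ/σ) × √(kept / 3.544 / 2) − 1.96].

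| s | Kept per arm | Kept in total | Power |
|---|---|---|---|
| 0% | 48 | 96 | 0.94 |
| 50% | 40.8 | about 82 | 0.90 |
| 100% | 33.6 | about 67 | 0.84 |

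Even the worst row stays above the minimum of 30 and above 80% power on the plan's inputs, taken here as given. Loss of power is not the main issue.

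**4. Bias, on assumed inputs**

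None of these inputs is in the article: true effects of 0.8, 0.6 and 0.5 SD at T1, T2 and T3; within-household correlation 0.5; 48 households per arm; withdrawal after T1, all of it unimputed. Where withdrawal depends on outcome, its log-odds change by 1 per SD of immediate gain. The target is the arm difference in T0-T3 change, truth 0.50 SD. Losses in the X-SIAGA arm are about 12%, 17% and 30%.

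| Withdrawal pattern | Complete-case estimate (SD) |
|---|---|
| Low gainers leave in the X-SIAGA arm only; control at random | 0.55, 0.57, 0.63 |
| Same dependence in both arms | about 0.50 throughout |
| High gainers leave in the X-SIAGA arm only | from about 0.45 down to about 0.38 |

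In the first pattern, 0.55 / 0.50 and 0.63 / 0.50 give inflation of about 10% to 26%. A likelihood analysis of all observed visits gives 0.50 at each loss level of that pattern.

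A separate simulation (true T3 difference 0.80 SD, about 30% dropout after T1, related to the T1 score in the intervention arm only) gives 0.93 SD for complete cases and 0.79 SD for a GEE on all available visits.

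**The case against.** The strongest reply has five parts.

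- **The GEE is also planned.** It compares the arms across time points and keeps the observed visits. This stands: a reader might infer that withdrawn households leave the between-arm comparison altogether, and the article does not support that. They leave one of two named analyses. Since neither is primary, the ANOVA could still carry the conclusion.
- **No sentence excludes households with a missing visit.** True. The closing sentence on ITT with imputed data could also mean wider imputation than LOCF for uncontactable dropouts. But the only rule written down is the narrow one.
- **Recovery and a sensitivity analysis are planned.** This stands in part. Recovery may rescue some missed visits, so not every household outside LOCF is lost. It cannot supply scores from a household that has withdrawn. Nothing says that the sensitivity analysis covers such households.
- **Rules for each type of missingness belong in an analysis plan that is not shown.** Fair as to detail, and their absence is not the point. The point is that the principle, imputation scope and model that the article does fix are inconsistent.
- **The size is assumed.** This stands. A reader might infer that deletion must inflate the effect of X-SIAGA. The working shows inflation, no bias or understatement, depending on the withdrawal pattern. Treating misses at T1, T2 and T3 as independent would also overstate the loss, because T1 follows directly after a one-day programme. With a 5% or 10% chance of a miss per visit, three visits give 1 − 0.95³ = 14% and 1 − 0.90³ = 27% of households deleted. Confining misses to T2 and T3 gives 1 − 0.95² = 9.8% and 1 − 0.90² = 19%.

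**Conclusion.** The concern holds in a limited form. For households that withdraw while contactable, and for missed visits that cannot be recovered, the repeated-measures ANOVA as described does not deliver the stated ITT approach. It discards visits that were observed, and it runs on a different set of households from the GEE.

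The exposure ranges from none to about 14 of 48 households per arm (48 − 33.6 = 14.4), depending on a contactable share that the article does not give. Neither the presence nor the direction of bias can be read from the article: both depend on whether withdrawal is related to outcome differently in the two arms. The 10-26% inflation is an illustration under one such pattern, not a forecast. The conclusion also assumes the classical form of repeated-measures ANOVA and no wider imputation than the rule stated.

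**What to change.** Replace the repeated-measures ANOVA as the between-arm analysis with a linear mixed model, available in the MIXED procedure of SPSS 26. Suggested wording:

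*All enrolled households are analysed in the arm to which their village was allocated. Every observed visit is used, whatever the reason for a missing visit (uncontactable, withdrawn or missed). The model has arm, visit and arm-by-visit terms, within-household correlation across visits, a village random effect, and a small-sample degrees-of-freedom correction for the eight villages.*

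If the repeated-measures ANOVA is kept, label it a complete-case secondary analysis and do not describe it as ITT.

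The cost is a change of wording, with the same data and software. The downside is that the model assumes data are missing at random, so missingness should be tabulated by arm, with reasons where participants choose to give them.
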